### Implementation evaluation

A multi-methods approach will be employed in the evaluation. Methods will involve quantitative and qualitative approaches embedded within continuous quality improvement. The evaluation will consist of formative, process, and outcome evaluations.

#### Formative evaluation

Formative (baseline) evaluation will include surveys of Organisational Readiness to Implement Change [35], Acceptability of Intervention Measure, Intervention Appropriateness Measure, and Feasibility of Intervention Measure [36], as well as a descriptive analysis of the indicators of the Tanahashi constructs listed in Table 1.

Guided by the Consolidated Framework for Implementation Research (CFIR) [37], the determinants (barriers and facilitators) of implementing routine screening and management of anaemia during pregnancy and postpartum will be evaluated using qualitative methods (Additional file 2). Furthermore, opportunities and strategies to improve implementation outcomes will be evolved using DIVA’s participatory approaches and focus group discussions (FGDs) involving implementers, patient representatives, policymakers, and researchers. We anticipate conducting 12 FGDs, each involving 8–12 participants. Key informant interviews with doctors, nurses, and other health workers (e.g. antenatal care, delivery, and postpartum officers at all health facility levels) will be conducted on a rolling basis until data saturation is achieved (a point in data collection when no additional issues or insights are identified from interviewing additional participants).

#### Process evaluation

Process evaluation will be conducted using the DIVA approach with the aid of the monitoring indicators described earlier. Furthermore, a process map will be developed as an output to communicate the understanding of the flow of patients as they transition across various facilities and levels of the health system to receive care from antenatal to postnatal periods and from screening for anaemia through the referral process to receiving various treatment options, including nutrition, medication, and IV FCM. The process map will also provide information about feasible services that can be delivered effectively across various categories of health facilities.

#### Outcome (summative) evaluations

Outcome evaluations will be conducted at the end line of the study. The primary outcome of the impact evaluation will be the effective coverage measures (implementation fidelity) indicated in Table 1. The secondary outcomes will be a repeat of the surveys carried out at baseline to evaluate the change in measures. Patient satisfaction with the interventions will also be surveyed.

Qualitative summative evaluation will be conducted through interviews and FGDs with the same stakeholder groups listed under formative evaluation. The normalisation process theory (NPT) [38] will guide the interviews and discussions, which will seek to understand how IV FCM was implemented, embedded, and integrated into the health system for the routine management of anaemia in pregnancy and postpartum.

#### Data analysis

Descriptive analysis using frequencies and percentages will be performed on categorical variables, while a Shapiro–Wilk test of normality will be performed on continuous variables. Variables with a normal distribution (non-significant (*p* > 0.05)) will be presented as means with standard deviations, while non-normally distributed data will be presented as medians with interquartile ranges. Univariable and multivariable ordinal and binary logistic regression will be used to evaluate the determinants of categorical implementation outcomes. Simple and multiple linear regression analyses will assess the changes in continuous variables.

Qualitative data recorded from interviews and DIVA will be transcribed verbatim. Familiarisation with the audio recording and reflexive notes recorded during transcription will be carried out before the analysis. Transcribed data will be coded deductively (guided by the NPT and CFIR) [37, 38] and inductively to generate themes emerging from the data. We will use thematic and framework analysis to capture the underlying concepts and patterns.

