### Study setting

IVON-IS will be conducted in Lagos State, South West, Nigeria. Specifically, implementation outcomes will be tested in a cluster of six health facilities that have not yet been exposed to training or implementation related to the ongoing IVON trials. The facilities span public (government-owned) and private (individual/organisation-owed) sectors in the state. The cluster will include one tertiary hospital, two secondary hospitals, one comprehensive primary health centre (PHC) in the public sector, and two private hospitals with varied patient bases. The selected facilities will be in proximity and linked to the state’s existing referral process. The cluster will represent a sub-unit of the health system and reflect the points of antenatal and postnatal care for pregnant women. Indeed, in Lagos, public health facilities manage 27% of deliveries in the state, while private health facilities take up about 48% [27]. Using projected data from our ongoing IVON clinical trials, we estimate that we will screen about 4000 pregnant and postpartum women per annum and have approximately 400 women eligible for treatment for anaemia.

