Effective/quality coverage^a^	Implementation fidelity	The proportion of eligible women screened for anaemia who adhered to the post-screening plan (e.g. referral for treatment of diagnosed anaemia or prescribed nutritional supplements)	The proportion of women with anaemia who used the treatment option according to the prescribed plan (e.g. dose/duration)	The proportion of women eligible to receive the IV FCM for pregnancy and/or postpartum anaemia who were administered the infusion according to the protocols.

^a^Primary outcome of DIVA

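### The named regressions make no allowance for nesting in six facilities, so tests of facility-level determinants and of baseline-to-endline change can be anti-conservative

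*Protocol article*

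**What the plan says.** All references are to the protocol article.

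- **Design.** Under Study setting, "implementation outcomes will be tested in a cluster of six health facilities". Their composition is given there: "The cluster will include one tertiary hospital, two secondary hospitals, one comprehensive primary health centre (PHC) in the public sector, and two private hospitals". That is four public and two private facilities, with a single tertiary hospital and a single primary health centre (PHC).
- **Volume.** The same section gives a workload projection: "we estimate that we will screen about 4000 pregnant and postpartum women per annum and have approximately 400 women eligible for treatment for anaemia".
- **Outcomes.** Table 1 defines the indicators as proportions of women, or of health workers at each site. For FCM the effective-coverage indicator is the proportion of eligible women "who were administered the infusion according to the protocols". Effective coverage is the primary outcome of the end-line evaluation.
- **Surveys.** Under Outcome (summative) evaluations, "The secondary outcomes will be a repeat of the surveys carried out at baseline to evaluate the change in measures".
- **Models.** Under Data analysis, "Univariable and multivariable ordinal and binary logistic regression will be used to evaluate the determinants of categorical implementation outcomes", and "Simple and multiple linear regression analyses will assess the changes in continuous variables".

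The article does not list the covariates. It mentions no facility term, random effect, generalised estimating equation or robust standard error.

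**The concern.** Women treated in one facility share its staff, stock, workflow and referral links, and the quality-improvement cycles act through those same features. Their outcomes are therefore likely to be correlated. The models named are, in their ordinary form, models for independent observations. A univariable or simple model has one predictor, so it cannot carry a facility term beside the determinant under study.

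Three things can go wrong:

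1. A covariate that takes one value per facility, such as sector or level of care, has only six independent values behind it. An ordinary regression treats it as if it had hundreds.
2. A before-after comparison picks up facility-specific drift as if it were a common effect.
3. A woman-level determinant whose distribution differs between facilities can carry the facility's own effect.

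Level of care has a further limit. With one tertiary hospital and one PHC, no model can separate those tiers from the individual facilities. The study intends its lessons to inform scale-up across Nigeria, so false precision here would travel.

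**Working it through.** **No figure to reproduce.** The article gives no power calculation and no significance level for the regressions. The 4000 and 400 are workload projections. A two-sided 5% level is assumed below.

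**Inputs.** From Study setting: 6 facilities, about 4000 women screened and about 400 eligible for treatment per year. Spread evenly, m = 400/6 = 66.7 and m = 4000/6 = 666.7 women per facility. The ICC is not in the document; 0.01 to 0.05 is assumed.

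**Step 1: a facility-level covariate.** The design effect is DE = 1 + (m - 1) × ICC. The true standard error is √DE times the naive one. The actual rejection rate of a nominal 5% test is approximately 2 × [1 - Φ(1.96/√DE)].

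| m | ICC | DE | SE ratio | Effective N | Rejection, formula |
|---|---|---|---|---|---|
| 66.7 | 0.01 | 1.66 | 1.29 | 241 of 400 | 12.8% |
| 66.7 | 0.02 | 2.31 | 1.52 | 173 of 400 | 19.8% |
| 66.7 | 0.05 | 4.28 | 2.07 | 93 of 400 | 34.4% |
| 666.7 | 0.01 | 7.66 | 2.77 | 522 of 4000 | 47.9% |
| 666.7 | 0.02 | 14.31 | 3.78 | 279 of 4000 | 60.4% |
| 666.7 | 0.05 | 34.28 | 5.86 | 117 of 4000 | 73.8% |

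A beta-binomial simulation (20,000 runs, four public against two private facilities, outcome rate 0.5) gave 12.8%, 20.0% and 34.4% at the smaller size and 48.0%, 60.8% and 74.6% at the larger. Repeat simulations reached 35% and 75% at the top of each range. With one assumed unequal spread of the 400 women, rejection was still 11-30%.

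**Step 2: a covariate balanced within facilities.** In the same simulation, with the ICC taken up to 0.10, the naive test rejected 4.0-4.9% of the time. There is no inflation here.

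**Step 3: baseline-to-endline change in a coverage proportion.** Let r be the correlation of a facility's effect between the two periods, with m women per facility per period. The variance of the change, relative to the naive variance, is D = 1 + (m - 1) × ICC - m × ICC × r. For m = 66.7, ICC 0.02 and r = 0.8, D = 1 + 1.31 - 1.07 = 1.25, which gives rejection of 7.9%.

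| r | m = 66.7, ICC 0.02 to 0.05 | m = 666.7, ICC 0.02 to 0.05 |
|---|---|---|
| 0.8 | 8-12% | 30-48% |
| 0.9 | 6-8% | 20-34% |
| 1.0 | 4-5% | 4-5% |

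Simulations at r = 0.8 gave 8-13% and 26-47%. The result depends strongly on r, which the document does not give.

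**Step 4: does the remedy hold its level?** A t-test on six facility-specific log-odds changes (5 df) rejected about 5% of the time. Facility fixed effects alone did not protect the period test: at r = 0.8 it still rejected 7.6-11.8% (m = 67) and 29-46% (m = 667). A t-test on facility proportions for four against two facilities (4 df) held 4.9-5.3%, but 4 df leaves little information for a facility-type contrast.

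**The case against.** The strongest reply is that this is inferred from silence. The article names model families in two sentences, never says that rows are independent, and condenses a fuller plan in which facility terms may appear. Multivariable regression does not exclude facility as a covariate. This stands in part: the finding concerns the models as named, and a fuller document may already resolve it. It does not dispose of the point, because the article commits to univariable and simple models, which leave no room for facility.

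Four stronger readings are tempting, and the documents do not support them.

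- **That every standard error is too small.** Step 2 shows otherwise for covariates balanced within facilities, and many woman-level or staff-level determinants may be close to that.
- **That the plan tests facility type by regression.** It never names tier or sector as a determinant. The phrase "feasible services that can be delivered effectively across various categories of health facilities" describes what the process map will inform. The private-public contrast above is an illustration of what happens if such a covariate is entered.
- **That ignoring pairing in the repeat surveys narrows the intervals.** Positive within-person correlation works the other way: treating pairs as independent makes intervals too wide. With an assumed 60 pairs and correlation 0.5, a nominal 5% test rejected 0.5% of the time. The article also does not say that the same individuals are surveyed again.
- **That the period-change rates describe a stated analysis.** Linear regression is assigned to change in continuous variables; no logistic test of change in coverage is described. Step 3 shows what an unadjusted test would do.

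It is also fair that this is a quality-improvement study with no stated power calculation or confirmatory hypothesis, which limits the severity.

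**Conclusion.** The point holds in a limited form. As named, the regressions do not allow for six facilities. If run that way, tests of any facility-level determinant are anti-conservative, with rejection of about 13-35% at 67 women per facility and about 48-75% at 667. Tests of baseline-to-endline change can be anti-conservative too, by an amount running from nothing to large according to the between-period correlation. Woman-level determinants can be confounded by facility.

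These sizes rest on an assumed ICC of 0.01 to 0.05, an assumed two-sided 5% level, one year's projected volume and, in the main calculation, an even spread of women over facilities. They cannot be worked out for the staff surveys, because staff numbers are not given. The inseparability of the tertiary and PHC tiers from their single facilities needs no such assumption. Severity: should-fix.

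**What to change.** 1. Include facility as a fixed effect (five indicators) in every woman-level and staff-level determinant model, and replace the univariable models by one-determinant models adjusted for facility. Facility-level covariates then drop out of these models, as they should.
2. Test baseline-to-endline change on the six facility-level changes, with a t reference on 5 df, wherever a non-zero baseline exists. Item 1 does not protect this comparison. With six clusters, robust standard errors or generalised estimating equations without a small-sample correction would not be reliable.
3. Report FCM indicators that have no usable baseline by facility at endline. The facilities are chosen as not yet exposed to FCM implementation under the IVON trials, so baseline log-odds are likely to be undefined.
4. Report tier and sector contrasts descriptively, facility by facility.
5. If the same staff are surveyed again and can be linked, analyse within-respondent change, keeping facility in the model.

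If a fuller plan already specifies an allowance for facility, a sentence saying so is enough, provided the method is suited to six clusters. The change is to analysis wording only; item 5 applies only where linkage exists. The cost is wider intervals, low power for period change on 5 df, and no inferential claim on facility tier.

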## Discussion

The IVON-IS is a novel study in Africa. Complementary to the IVON and IVON-PP clinical trials, the IVON-IS seeks to routinise the use of an IV iron formulation by overcoming contextual and systemic barriers using continuous quality improvement.

While misconceptions around the use of IV iron formulations are global, systemic constraints to use may be contextual [10]. Thus, this study provides an opportunity to contribute to both contextual and generalisable knowledge on the adoption and administration of FCM in the management of obstetric cases of iron deficiency anaemia. The study not only focuses on the endpoint but also seeks to improve the continuum of care related to obstetric anaemia. Routine nutrition prescriptions and practices, health promotion, screening for anaemia, and referral processes will also be strengthened.

The study will throw light on health system constraints to address the highly prevalent problem of obstetric anaemia in Nigeria, which contributes to the high maternal and infant morbidity and mortality. Furthermore, the study is expected to evolve transferable knowledge on addressing these bottlenecks within context. Thus, lessons from this IVON-IS study will inform scale-up across Nigeria and the adoption of the interventions and strategies across other African countries.

The methods and strategies used in this study will contribute to the body of knowledge in both implementation and improvement sciences applicable to LMICs. The Deming Cycle or PDSA is considered an intervention in improvement science but a method or strategy in implementation science [39, 40]. Thus, the PDSA is viewed as an intersection between both disciplines [40]. This four-step iterative technique is often used to solve problems and improve organisational processes [41]. In contrast, however, the DIVA model used in the IVON-IS study, though an adaptation of the PDSA, is designed to improve the implementation of interventions within complex health systems common in LMICs [39]. Incorporating the Tanahashi health systems evaluation model into DIVA provides an opportunity to apply systems thinking in quality improvement. This approach also strengthens the decentralised evolution of change strategies towards adoption and optimal implementation of new interventions within existing health system structures and processes. It is hoped that lessons learned from the methodological approach used in the IVON-IS will contribute to building capacity and advancing the application of implementation science to strengthen health systems in Africa and beyond.

## Data Availability

Not applicable.

## Abbreviations

CFIR: Consolidated Framework for Implementation Research
DIVA: Diagnose-Intervene-Verify-Adjust
FCM: Ferric carboxymaltose
FGD: Focus group discussion
Hb: Haemoglobin
IMT: Implementation Management Team
IVON: Intravenous Versus Oral Iron-Antepartum Trial
IVON-IS: Intravenous Versus Oral Iron-Implementation Study
IVON-PP: Intravenous Versus Oral Iron-Postpartum Trial
LMICs: Low- and middle-income countries
NPT: Normalisation process theory
PDSA: Plan-Do-Study-Act
